# A comparison of standard occupational therapy versus early enhanced occupation-based therapy in a medical/surgical intensive care unit: study protocol for a single site feasibility trial (EFFORT-ICU)

**DOI:** 10.1186/s40814-021-00795-2

**Published:** 2021-02-18

**Keywords:** Critical care, Mechanical ventilation, Rehabilitation, Occupational therapy, Delirium, Cognition

## Abstract

**Background:**

Admissions to intensive care units (ICUs) are increasing due to an ageing population, and rising incidence of cardiac and respiratory disease. With advances in medical care, more patients are surviving an initial stay in critical care; however, they can experience ongoing health and cognitive limitations that may influence return to baseline function up to a year post-admission. Recent research has focused on the introduction of early rehabilitation within the ICU to reduce long-term physical and cognitive complications. The aim of this study is to explore the feasibility and impact of providing early enhanced occupation-based therapy, including cognitive stimulation and activities of daily living, to patients in intensive care.

**Methods:**

This study involves a single site randomised-controlled feasibility trial comparing standard occupational therapy care to an early enhanced occupation-based therapy. Thirty mechanically ventilated ICU patients will be recruited and randomly allocated to the intervention or control group. The primary outcome measure is the Functional Independence Measure (FIM), and secondary measures include the Modified Barthel Index (MBI), Montreal Cognitive Assessment (MoCA), grip strength, Hospital Anxiety and Depression Scale (HADS) and Short-Form 36 Health survey (SF-36). Measures will be collected by a blind assessor at discharge from intensive care, hospital discharge and a 90-day follow-up. Daily outcome measures including the Glasgow Coma Scale (GCS), Richmond Agitation and Sedation Scale (RASS) and Confusion Assessment Measure for intensive care units (CAM-ICU) will be taken prior to treatment. Participants in the intervention group will receive daily a maximum of up to 60-min sessions with an occupational therapist involving cognitive and functional activities such as self-care and grooming. At the follow-up, intervention group participants will be interviewed to gain user perspectives of the intervention. Feasibility data including recruitment and retention rates will be summarised descriptively. Parametric tests will compare outcomes between groups. Interview data will be thematically analysed.

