### Aims and objectives

The aim of this study is to explore the feasibility and impact of providing early enhanced occupation-based therapy, including cognitive stimulation and activities of daily living, to patients in intensive care. The intervention will focus on cognitive stimulation and engagement in functional activities in mechanically ventilated patients within an intensive care setting. This will be explored through a pilot feasibility trial comparing standard care to daily early enhanced occupation-based therapy. It is hypothesised that critically ill mechanically ventilated patients who participate in the intervention will demonstrate increases in functional ability, cognition and participation compared to those patients who receive standard care. Feasibility aspects of the intervention to be investigated include whether occupational therapy can be provided consistently to a partially sedated population, as well as within a medical setting where environment and medical equipment may limit interventions.

The study is divided into two parts: Part 1 aims to investigate the feasibility of early enhanced occupation-based therapy in a medical/surgical intensive care unit. Part 2 aims to explore the perceptions of participants and their significant others in relation to the therapy experience. Both parts of the study are carried out concurrently.

Specifically, the objectives of the early enhanced occupation-based therapy (the intervention) are:

Part 1:
To evaluate the utility of a selection of functional, cognitive, physical and quality of life outcome measures in their ability to capture the effect of the intervention on participants and their long-term outcomes.To identify recruitment and consent rates from eligible participantsTo evaluate retention rates in response to follow up procedures (attendance at interviews)To test the intervention in terms of therapist compliance, ability to provide consistent intervention (fidelity), differentiation from current usual practice and amount of staff skill/experience required to carry out the interventionTo explore the effect of the intervention on occupational performance at intensive care and hospital discharge, and to evaluate the effect on cognitive, functional and mood factors on discharge from the intensive care unit and hospital, and at 90 days post-randomisation.

Part 2:

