### Outcome measures

#### Primary outcome measure

Independence within activities of daily living will be measured using the Functional Independence Measure (FIM™). The FIM will quantify the participant’s functional and cognitive status at intensive care unit and hospital discharge, as well as at 90 days post-randomisation. This tool is validated for use in the critically ill population [60, 61] and provides reliable information regarding patient functional change during rehabilitation across various hospital and community settings [62]. The FIM will be conducted within 24 h of the expected discharge from the intensive care unit and hospital or on the Friday before the expected discharge, if likely to occur over the weekend. It will also be administered during the 90-day follow-up session. The FIM will be performed by an occupational therapist blinded to participant assignment groups and who does not actively work on the intensive care unit.

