### Sample size

A sample size of 30 participants has been chosen, based on recommendations regarding pilot and feasibility trials evaluating outcomes [77]. Fifteen patients from the intervention group will be included within the qualitative component carried out at 90 days post-randomisation.

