### Data analysis

All data from the case report forms (CRF) will be entered into a purposefully designed Excel database and exported into SPSS version 22.0 for analyses. Descriptive statistics will be used to determine the distributions of the data for the intervention and control groups and to test whether statistical assumptions for parametric tests are achieved. Imputation will be used to correct for missing data. Continuous variables that are normally distributed will be compared between the groups at each follow-up using an independent groups *t* test. Effect sizes will be calculated using Cohen’s *d*. Non-parametric analysis will be conducted for continuous variables that are not normally distributed. Categorical variables will be compared with the chi-square statistic. A *p* value of 0.05 will be considered statistically significant. Where appropriate, analyses will be reported with mean differences and 95% CI. Previous values from the same patient will be used for missing data.

In particular, objectives will be analysed as follows:
The utility of the selection of outcome measures will undergo sensitivity analyses in relation to the ease with which they can be administered and will relate to missing data and the identification of both univariate and multivariate outliers. The effect size for the primary outcome variable will be used to determine the required sample size for a fully powered trial.Recruitment and consent rates will be collected and analysed to determine the feasibility of recruiting form the chosen population. The inclusion and exclusion data (screening log) will be summarised and will influence further protocol changes when considering progression to a full scale randomised controlled trial.Retention rates in response to follow-up procedures (attendance at interviews) will be analysed to identify any trends that may influence further trial progression.The intervention data will undergo sensitivity analyses in relation to non-compliance, the intention to treat per protocol in addition to as treated. Protocol violations regarding the intervention manual strategies will be noted.The intervention effect will be analysed through the use of the above outcome measures, and further analysis of case notes will reveal common trends in treatment adaptation or selection, based on the structure of the intervention manual.

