## Discussion

Early rehabilitation within critical care units has been shown to be effective in multiple studies [17, 24]; however, the occupational therapy approaches to enhance long-term recovery require further investigation especially in mechanically ventilated patients. This trial aims to explore the feasibility of providing occupational therapy to mechanically ventilated patients in a critical care setting. It aims to identify approaches that may be beneficial to patients and family members surviving a critical care stay, as well as defining where priorities in service provision may lie. The ability to optimise recovery with clearer multidisciplinary input may strengthen future collaboration to drive an early rehabilitation model. Analysis of day to day therapy provision, the ability to adapt and engage patients along a continuum of sedation and immobilisation variables will provide clarity about the types of interventions that are best completed in the critical care setting by an occupational therapist. While this study is not powered to detect clinically significant change, it will provide information that will enable the design of a phase III trial including sample size calculations. A dissemination plan has been developed that includes publication in peer-reviewed journals, webinars and conference presentations and posters.

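### FIM is the primary outcome and is tested at 0.05 in a feasibility trial not powered for it, while the progression criteria use no FIM score or effect

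*Protocol article*

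**What the plan says.** Purpose. The overall aim is twofold: "The aim of this study is to explore the feasibility and impact of providing early enhanced occupation-based therapy" (Aims and objectives). The same section narrows this for the randomised comparison: "Part 1 aims to investigate the feasibility of early enhanced occupation-based therapy in a medical/surgical intensive care unit". It also states a directional hypothesis, that treated patients "will demonstrate increases in functional ability, cognition and participation compared to those patients who receive standard care".

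Primary outcome. The abstract says "The primary outcome measure is the Functional Independence Measure (FIM". The Primary outcome measure section agrees ("Independence within activities of daily living will be measured using the Functional Independence Measure") and schedules FIM at ICU discharge, hospital discharge and 90 days after randomisation, with none of the three singled out. Feasibility data are to be summarised descriptively (abstract) and are not designated primary.

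Analysis. Normally distributed continuous outcomes get an independent-groups t test at each follow-up, others a non-parametric test; a p "value of 0.05 will be considered statistically significant" (Data analysis). Cohen's d and, where appropriate, mean differences with 95% CIs are also planned, and the FIM effect size is meant to set the sample size of a full trial.

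Size and power. "A sample size of 30 participants has been chosen, based on recommendations regarding pilot and feasibility trials evaluating outcomes" (Sample size), with 1:1 allocation. The Discussion adds: "While this study is not powered to detect clinically significant change".

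Progression. Table 1 has five rows: recruitment, retention, completion of the intervention, acceptability of the outcome measures, and serious therapy-related adverse events. The acceptability row asks whether 80% of the measures can be administered at each time point.

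**The concern.** The label of primary outcome and the decision rule point at different things. The label, the hypothesis and the 0.05 threshold belong to an efficacy trial; the title, the Part 1 aim, the sample size rationale and Table 1 belong to a feasibility trial. The primary outcome normally leads the report.

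Two misreadings become possible. A non-significant FIM comparison, which is likely unless the effect is very large, could be taken as a failed trial even if every feasibility criterion is met. A significant one, by chance or otherwise, could be taken as evidence of benefit from a study that says it cannot provide it.

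**Working it through.** **Can the sample size be reproduced?** No. The article gives no effect size, SD or power for the 30 patients; it relies on pilot-trial recommendations. The check is therefore what a FIM test could show with that number.

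**Inputs from the article.** 30 patients at 1:1, so 15 per arm. Significance level 0.05. Table 1 retention: 75% to proceed (15 × 0.75 = 11.25, about 11 per arm) and 50% as the floor (15 × 0.50 = 7.5, about 7 per arm). Three FIM time points.

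**Assumptions.** Two-sided testing (sidedness is not stated, but 95% CIs are planned) and a standardised difference d from 0.3 to 0.8.

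**Power.** For a two-sample t test with n per arm, df = 2n − 2 and noncentrality = d × √(n/2). For n = 15 and d = 0.5, noncentrality = 0.5 × √7.5 = 1.37 on 28 df, giving power 0.262.

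| n per arm | d = 0.3 | d = 0.5 | d = 0.8 | d needed for 80% power |
|---|---|---|---|---|
| 15 (no loss) | 12% | 26% | 56% | 1.06 |
| 11 (75% retained) | 10% | 20% | 43% | 1.26 |
| 7 (50% retained) | 8% | 14% | 28% | 1.63 |

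**False positives for FIM.** With three tests at 0.05 and no effect, the chance of at least one significant result is 1 − 0.95³ = 0.143 if the tests are independent. Repeated FIM scores in the same patients should be positively correlated, which lowers it.

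**What the FIM estimate can carry.** The large-sample SE of d is √(2/n + d²/(4n)). For an observed d = 0.5 at n = 15: √(2/15 + 0.25/60) = √0.1375 = 0.371, so the 95% CI is 0.5 ± 1.96 × 0.371, or −0.23 to 1.23. At 80% power (normal approximation), the implied total for a full trial is 126 at d = 0.5 and 22 at d = 1.23; it is undefined at the lower limit because the interval includes zero. The effect size therefore sizes the next trial only loosely, and a p-value adds nothing to it.

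**What a feasibility criterion can carry.** As an illustration, 23 of 30 retained (77%) has a 95% Wilson CI of 59% to 88%. That can be read directly against the 75% and 50% cut-offs: compatible with either side of the upper one, and clear of the lower.

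**Table 1 against FIM.** Four rows do not involve FIM. The fifth involves it only as one of the measures to be administered. No row depends on a FIM score, difference or p-value.

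**The case against.** The strongest reply is that FIM has a proper place here. The aim includes impact as well as feasibility; the Part 1 objectives include exploring the effect on occupational performance and judging which measures can capture it; and the FIM effect size is to size the next trial. On that view, primary outcome measure is shorthand for the lead clinical measure. A progression table that ignores efficacy results is sensible in an unpowered trial. The article also has safeguards: pre-stated progression criteria, reporting under the CONSORT extension for pilot and feasibility trials, the admission about power, and planned effect sizes and CIs.

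Much of this stands. A reader might infer that Table 1 leaves FIM out altogether; it does not, because the acceptability row covers whether FIM can be administered. A reader might infer that FIM serves no stated objective; it serves two, though imprecisely. A reader might also count every scheduled measure (FIM, MBI, MoCA, grip strength and HADS at three time points, SF-36 at two: 17 tests) and conclude that a false positive is more likely than not, at 1 − 0.95¹⁷ = 58%. That figure assumes one score per instrument, which the article does not specify, and independence among overlapping measures in the same patients. It also does not bear on the designation of FIM. Finally, the misreadings are a risk; the article does not say that the conclusion will rest on a FIM p-value.

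None of this calls for a significance threshold. Exploring impact and planning a later trial need an estimate with its interval, and an admission in the Discussion does not withdraw the rule in Data analysis or the label in the abstract and Methods.

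**Conclusion.** The point holds for FIM results: the designated primary outcome carries a 0.05 rule in a trial that disclaims power, and no FIM score or effect enters the decision the trial exists to inform. A FIM p-value cannot settle feasibility, and it cannot reliably settle efficacy.

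The size rests on two-sided alpha 0.05, a t test and assumed d values. A full-retention analysis is more likely than not to miss a true d of 0.5, and reaching 80% power takes a difference of more than one SD. The 14% figure for three FIM tests is an independence value.

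The documents do not support the stronger conclusions that the trial cannot answer its question, or that the result will be misread. The design already contains what is needed to answer the feasibility question; the labels and the threshold put the emphasis elsewhere. This should be corrected, but it does not invalidate the trial.

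**What to change.** 1. Designate the Table 1 feasibility criteria as the primary outcomes and base the conclusion on them. First give the acceptability row distinct thresholds: its text is now the same in all three columns, so it cannot separate proceeding from stopping.
2. Label FIM the candidate primary outcome for the phase III trial.
3. Report FIM and the other clinical outcomes as exploratory, with mean difference and 95% CI, and remove the 0.05 decision rule for them. Present the directional hypothesis as one for the later trial.

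Cost: rewording of the abstract, aims, outcome and analysis sections. The Ethics/governance section requires ethics committee approval for changes to outcomes, and communication to all investigators and the registry. Trial status says that the trial has been recruiting and is paused, and the research team is not blinded, so the amendment should give its reasons and state that it was made after recruitment began and before any outcome analysis. The investigators must confirm the latter; Data collection places analysis after trial completion. No new data are needed. The downside is that no significance claim can be made for FIM.

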**Discussion:**

This trial will provide information about the feasibility of investigating how occupational therapy interventions in ICU influence longer term outcomes. It seeks to inform the design of a phase III multicentre trial of occupational therapy in critical care general medical intensive care units.

**Trial registration:**

Australia New Zealand Clinical Trials Registry (ANZCTR): ACTRN12618000374268; prospectively registered on 13 March 2018/https://www.anzctr.org.au

Trial funding: Metro South Health Research Support Scheme Postgraduate Scholarship

**Supplementary Information:**

The online version contains supplementary material available at 10.1186/s40814-021-00795-2.

## Background

Admissions to intensive care units within Australian hospitals have increased over the last 10 years with approximately 161,000 patients requiring a stay in an intensive care unit between 2017 and 2018 [1]. The long-term burden of care and admissions requirements may also change in accordance with unpredictable disease presentations and an increasing requirement of health care service provision.

Patients admitted to an intensive care unit may experience a lack of control, reduction in sensory stimulation and reduced engagement in meaningful activities [2], in addition to being subjected to intrusive interventions. Subsequently, patients may develop a sequelae of cognitive and physical symptoms known as post-intensive care syndrome (PICS), often accompanied by reduced long term participation outcomes [3, 4]. Longitudinal studies on critical illness survival show that 30–80% of patients will acquire PICS, characterised as a collection of complications including persistent cognitive dysfunction, acquired weakness and post-traumatic stress disorder [5, 6]. A substantial proportion of patients who survive their initial critical care stay report significant decreases in quality of life at 3–6 months post admission [4, 7] in addition to increased mortality and associated economic costs [8–10], especially in the presence of acute respiratory distress syndrome (ARDS) [11].

Early rehabilitation within critical care settings is now considered effective and feasible when carried out within a multidisciplinary approach [12–16] following successful pioneering studies first conducted in 2009 [17, 18]. Yet while physical rehabilitation and early cognitive stimulation addressing delirium management have been shown to be effective [12], to date, there remains limited evidence regarding the impact of early task-specific training carried out by occupational therapists directed towards cognitive and functional engagement within the intensive care setting [19]. Altering the approach to rehabilitation through participation in meaningful cognitive and functional tasks such as activities of daily living rehabilitation may lead to further long-term benefits. Critical care practice has not traditionally included occupational therapy engagement in functional tasks or early self-care rehabilitation; thus, there is a growing need for early effective interventions addressing cognitive, physical and psychological functioning to optimise long-term functioning [20]. While occupational therapy service delivery and role in intensive care units may vary between critical care settings [19, 21], its relevance and impact remains supported by a recent systematic review [22] and continues to be explored with respect to scope of practice and benefits [23]. Costigan et al. [19] in their scoping review note that occupational therapy interventions in the intensive care remain dominated by physical rehabilitation (splinting, positioning) and less by practice of activities of daily living. This feasibility trial will consider splinting and positioning as standard usual care and introduce occupation-based therapy (using activities of daily living practice) as the intervention for comparison.

A recent study by Alvarez et al. [24] demonstrated the effectiveness of occupational therapy for managing delirium in non-mechanically ventilated patients and provided a basis for the introduction of occupational therapists as core multidisciplinary team members to address intensive care unit-related disorders during recovery. However, there is an ongoing need for research into the feasibility and effectiveness of graded occupation-based activities within the intensive care unit for patients who are mechanically ventilated. Howell [2] provided an approach for delivering self-care tasks to patients in intensive care. Howell proposed that, through participation in structured and graded purposeful activities and occupations, the reticular activating system which controls the brain’s ability to interpret and respond to stimuli is challenged such that a state of sensory overload or sensory deprivation is avoided [2]. Appropriately challenging activities lead to positive cognitive and sensory stimulation, which affects long-term participation by improving physical strength and functional ability [2]. Participation in purposeful activities and task-specific training is supported by multiple publications [25, 26], including three reviews [27–29], that address various aspects of task-specific training delivery and encourage the use of structured and individualised activities of daily living as a therapeutic medium. The majority of supportive literature relates to the diagnosis of stroke, with a Cochrane review [30], finding that patients who participate in occupational therapy interventions are less likely to deteriorate and more likely to gain higher levels of independence in activities of daily living. Support for the introduction of task-specific training in distinct populations such as Alzheimer’s disease [25] and total hip replacement [26] leads to varying results; however, the paucity of literature does not reflect usual clinical practice. Meaningful activities improve cortical reorganisation, which in addition to regular practice and sufficient intensity, impact significantly on recovery within the domain of self-care [31]. The literature may focus predominantly on the stroke population [32], yet these concepts may be transferable to patients who endure an intensive care admission, due to higher exposure to mechanical ventilation, ongoing sedation and subsequent prolonged bed rest leading to weakness. Task-specific training can therefore be defined as “training which utilises, as its principal therapeutic medium, ordinary everyday activities which are intrinsically and/or extrinsically meaningful to the patient” (pg. 181) [33], and often includes activities of daily living or occupation-based therapy.

Engagement in functional rehabilitation activities within the critical care setting needs to be explored further. While the critical care patient cohort is often unwell, integrating rehabilitation and participation within the limits of their medical stability has beneficial effects from a user perspective to offset the feelings of anxiety, loneliness and fear when mechanically ventilated [34, 35]. There is limited evidence exploring the patient perspective on participating in structured rehabilitation however exploration of factors such as diary use [36], humanisation of nursing environments [37] and relatives’ experiences of intensive care admissions [38] support a qualitative approach towards understanding factors that may influence participation in occupation-based therapy.

